The patient will be placed in a dorsal position for cardiac monitoring, noninvasive blood pressure measurement, and pulse oximetry. The nasal fossae will be lubricated with 2% topical lidocaine gel, followed by the introduction of nasopharyngeal catheter number 08 to provide supplemental oxygen. Fentanyl (0.5-2 μg/kg) and midazolam (0.03-0.05 μg/kg) will be administered intravenously to achieve light sedation. Propofol bolus (20-40 mg/dose) may be used to achieve the desired sedation. Next, the custom nasal mask of CPAP will be attached to the patient’s face, allowing the passage of the video-bronchoscope (Standard Q180 Olympus) with an external diameter of 4.9 mm and a working channel of 2.0 mm. Topical lidocaine at a dose of 1% without a vasoconstrictor (maximum dose of 7 mg/kg) will be instilled in the larynx and tracheobronchial tree. This will be followed by secretion aspiration. Subsequently, the presence of fixed or dynamic tracheal and bronchial collapse during the respiratory cycle will be analyzed and recorded. Direct observational assessment will be defined at the site with the greatest tracheal collapse and main bronchi during inspiratory and expiratory normal ventilation. Patients who do not present significant airway collapse will be excluded from the next step.

#### Stage 2

To evaluate the reduction of airway collapse, the bronchoscope will be fixed with the aid of a customized catheter in the tracheal region at least 2 cm before the area of the greatest collapse, previously defined by three bronchoscopists present in the examination room. The CPAP titration will start with a pressure of 0 cm H2O and be gradually increased in steps by 2 cm H2O every 10 complete respiratory cycles until a pressure of 18 cm H2O is reached (Figure 1).

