**Figure 1 figure1:**
[figure not shown]
Bronchoscopic view of the trachea and the catheter (blue). Trachea during 0 cm H2O pressure during inspiration (A) and during expiration (B). Trachea in 18 cm H_2_O pressure during inspiration (C) and expiration (D)

 Through observational analysis and after a complete consensus among the bronchoscopists is reached, the minor pressure capable of reducing the degree of collapse in the trachea will be defined (P1). This procedure will be repeated in the main bronchus presenting major collapse. The entire procedure will be documented through video recording, and the images will be analyzed with software assistance (Image Processing Toolbox, Matlab). Measures in the airway variation area will be analyzed by comparing the area of collapse at 0 cm H2O pressure with the corresponding measurements at different applied pressures titrated during the procedure. This analysis will allow us to find the pressure that reduces the degree of airway collapse (P2) [42,43]. EIT will be used for impact analysis of different pressures on pulmonary ventilation (distal airways), a functional imaging method that uses low-intensity electric currents. EIT can dynamically evaluate regional pulmonary ventilation by analyzing impedance variations and minimum impedance in a given thoracic segment by reproducing them in two-dimensional images. It is a noninvasive method that does not use ionizing radiation [44-47].

The EIT data will be acquired using ENLIGHT (Timpel), which produces 50 images per second, sampled in real time [44-47]. Distribution of ventilation will be analyzed at each CPAP level during the positive and expiratory pressure (PEEP) titration maneuver by dividing the EIT image into 4 quadrants (regions of interest, ROI), 2 of which will be gravity dependent (lower lobes) and 2 will be gravity independent (upper lobes). In patients who present tracheomalacia during bronchoscopy, a chest CT will be performed at visit 3 during inspiration and forced expiration in the presence or absence of CPAP. The ideal pressure for this will be obtained during bronchoscopy with an aim to evaluate and document the reduction of tracheal collapse. The images will be obtained by multislice tomography. No intravenous contrast will be administrated.

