## Discussion

Thus far, the main finding of this study is the identification of the progressive increase in the degree of pressure that can reverse the collapse of the trachea and bronchi and stabilize the airway.

MKS or congenital TBM is a rare and poorly studied disease. It has a wide spectrum of signs and symptoms and can have a great impact on the quality of life. Dyspnea, accumulation of secretions in the airways, bronchiectasis, and recurrent respiratory infections increase the morbimortality of the disease.

There is no consensus on the best treatment. In general, measures extrapolated from other pulmonary pathologies, such as those employed in chronic obstructive pulmonary disease and bronchiectasis, are used for therapeutic management. Among the specific treatments currently available, we want to highlight the endotracheal and endobronchial prosthesis and tracheobroncoplasty surgery. However, both approaches have limited results and are associated with frequent complications.

There is a rationale for the use of positive pressure. The use of positive pressure could maintain the patency of the collapsed airways, thereby providing a “pneumatic stent,” which in turn could reduce airflow obstruction and promote mobilization of secretions within the airways. However, no study protocol has been performed to test this hypothesis.

The goal of this study is to assess if positive pressure with CPAP can be applied to reduce the extent of airway collapse and improve ventilation in MKS patients with tracheobronchomalacia. At the same time, we will evaluate the prevalence of OSAHS, a related and frequently occurring comorbidity that contributes to the worsening quality of life of patients with MKS.

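### Within each bronchoscopy run pressure only rises from a single opening 0 reading, so CPAP effect on airway area is fully aliased with elapsed time and sedation, and P1 is read by apparently unmasked raters

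*Protocol article*

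**What the plan says.** The protocol article (Methods, Study Design, Stage 2) fixes the sequence. "The CPAP titration will start with a pressure of 0 cm H2O", and pressure is then "gradually increased in steps by 2 cm H2O every 10 complete respiratory cycles until a pressure of 18 cm H2O is reached". For the second site, "This procedure will be repeated in the main bronchus presenting major collapse". No descending limb, replicate or return to 0 within a site is described.

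Two pressures come out of this.
- P1 is a visual judgement in the examination room: "Through observational analysis and after a complete consensus among the bronchoscopists is reached", the lowest pressure that reduces collapse is named.
- P2 comes from software-assisted area measurement of the video, "comparing the area of collapse at 0 cm H2O pressure with the corresponding measurements at different applied pressures titrated during the procedure".

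EIT is recorded at the same time as bronchoscopy. Stage 1 describes light sedation with fentanyl and midazolam and adds: "Propofol bolus (20-40 mg/dose) may be used to achieve the desired sedation". The trial is open-label with one arm. Statistical Analysis plans a two-way repeated-measures ANOVA with Tukey or Sidak post hoc tests at a 0.05 level, and has no sample size calculation. The Discussion reports that so far "the main finding of this study is the identification of the progressive increase in the degree of pressure that can reverse the collapse".

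**The concern.** With no control arm, the bronchoscopic evidence for an optimal pressure is each patient's change from the opening 0 reading. Every higher pressure is also a later time. Depth of sedation, breathing effort, secretions and adaptation to the mask can all change over the minutes of a run. Such a change would be read as a pressure-response if it went towards less collapse, and would hide one if it went the other way. P1, P2 and the ANOVA on airway area all depend on this contrast.

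P1 carries a second risk. Three bronchoscopists in the room agree on it openly, in a sequence that they know can only go up. Even without sight of the pressure display they could tell that a later view means a higher pressure. Consensus without prior independent readings also leaves no measure of how far they agreed.

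**Working it through.** The article states no power, SD or drift, so there is no figure to reproduce. Two checks apply.

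**1. Can pressure and time be told apart?**

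Levels: 0 to 18 by 2 gives 18/2 + 1 = 10. Breaths per site: 10 × 10 = 100. At an assumed 10 to 25 breaths/min, one run lasts 100/25 = 4 to 100/10 = 10 min.

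Code period order as t = 0, …, 9. Then pressure = 2t exactly, so the correlation is 1.00.

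| Data | Correlation of pressure with order | Rank, 10 levels + linear time |
|---|---|---|
| One site's run (airway area) | 1.00 | 10 of 11 |
| Both runs in sequence, second restarting at 0 (EIT) | 0.50 | 11 of 11 |
| One run plus one later 0 reading | 0.57 | 11 of 11 |

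The bronchial run does not help the airway-area series, because it images another site: neither site gets a second 0 within the titration. EIT images the thorax, so its two runs can be pooled. That gain assumes no separate shift between runs, for example from moving the scope. If a run effect is added, the model has rank 11 of 12 and time is again not estimable.

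**2. What would drift do to the planned test?**

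All inputs here are assumptions:
- no CPAP effect;
- the same linear drift in every patient, of 0.5 or 1 percentage point of collapse per step (4.5 or 9 points from first to last level);
- independent within-patient errors with SD 5 or 10;
- n = 10 (at least 15 patients are followed, and those without significant collapse do not enter Stage 2).

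The ANOVA is taken as patient by pressure level, with F on 9 and (n − 1) × 9 = 81 degrees of freedom. Its noncentrality is λ = n × b² × Σ(t − 4.5)² / SD², where b is the drift per step and Σ(t − 4.5)² = 82.5.

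| Drift per step | SD | λ | Chance of p < 0.05 |
|---|---|---|---|
| 0.5 | 10 | 10 × 0.25 × 82.5 / 100 = 2.06 | 12% |
| 0.5 | 5 | 10 × 0.25 × 82.5 / 25 = 8.25 | 42% |
| 1 | 10 | 10 × 1 × 82.5 / 100 = 8.25 | 42% |
| 1 | 5 | 10 × 1 × 82.5 / 25 = 33 | 99% |

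With no drift the rate is 5%. In units of the within-patient SD, a simulation (4,000 runs per cell) of a total drift of 0.5, 1 and 1.5 SD gave 11%, 41% and 82% at n = 8, and 19%, 75% and 99% at n = 15. A linear-trend test would react more strongly (25% to 73% at 0.5 point per step), but it is not the planned analysis.

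**The case against.** Several points on the other side are sound.

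- **The run is not the only evidence.** Visit 3 adds CT in inspiration and forced expiration with and without CPAP, an on/off contrast outside the ascending sequence. A reader might infer that the trial as a whole cannot separate CPAP from time; the article does not support that. The check is limited, however: one pressure, a different breathing manoeuvre and no stated order. The abstract offers CT to patients who showed a reduction in collapse, whereas Stage 2 gives it to patients with tracheomalacia. These statements must be reconciled. Restricted to responders, CT could not test the result that selected them. In neither form can it validate a pressure-response, P1 or P2.
- **EIT may hold its own check.** If the bronchial run restarts at 0, EIT has a second 0 reading after 18 cm H2O, so the aliasing is not complete there.
- **Scope movement is addressed.** The bronchoscope is held by a customised catheter, so scope drift is a weak part of the argument.
- **Unmasked rating is inferred.** A reader might take it as stated that the raters know the pressure. The article never says so; it follows from the open-label design, their presence in the room and the fixed order. Expectation bears mainly on P1. P2 is software-assisted, and masking of that step may be set out in the full protocol. Nor does the early finding in the Discussion show that any reading was biased.
- **Drift is not documented.** No passage gives its size or direction. The propofol sentence stands in Stage 1, and the article does not say whether boluses are given during titration.

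None of this removes the aliasing in the airway-area data, which follows from the stated sequence alone.

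**Conclusion.** The concern holds for the airway-area series at each site, and so for P2 and the ANOVA on collapse. It also holds for P1, where apparently unmasked consensus adds to it. The aliasing is exact (correlation 1.00, rank 10 of 11) and needs no assumption beyond the stated sequence. No later modelling of one site's run can undo it.

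Its practical size is unknown. The range of about 12% to 99% false-positive results rests on assumed drift, SD, n = 10 and a common direction in all patients. It shows that modest drift could matter, not that drift occurred or that it favours CPAP. For EIT the problem is partial, and for the trial as a whole the visit 3 CT gives a limited independent check.

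**What to change.** Measurement and analysis changes, none of which alters the titration:

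1. Measure the recorded video clips in random order with the pressure label hidden. The whole procedure is recorded, so this can include patients already studied.
2. Have each of the three bronchoscopists write down P1 before the consensus discussion, and report their agreement. This is possible only for patients still to come.
3. Log the time of each sedative bolus against the pressure steps.
4. Analyse EIT over both runs with a time term, stating the assumption of no separate shift between runs.
5. State in the report that the pressure-response, P1 and P2 are confounded with time within a run.
6. Reconcile the abstract and Stage 2 on who has the visit 3 CT.

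Items 1 and 2 reduce rater bias. They do not remove the aliasing, which is why item 5 is needed.

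A repeat 0 reading at the end of a run would make linear time estimable (rank 11 of 11, correlation 0.57). It changes the procedure, so it is for the investigators to weigh and is not prescribed here. If it is taken, its difference from the opening 0 should be reported as drift plus carry-over from 18 cm H2O, and not interpolated as the reference.

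The cost is a little more clip handling and analysis, and a more cautious conclusion.

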**Figure 1 figure1:**
[figure not shown]
Bronchoscopic view of the trachea and the catheter (blue). Trachea during 0 cm H2O pressure during inspiration (A) and during expiration (B). Trachea in 18 cm H_2_O pressure during inspiration (C) and expiration (D)

 Through observational analysis and after a complete consensus among the bronchoscopists is reached, the minor pressure capable of reducing the degree of collapse in the trachea will be defined (P1). This procedure will be repeated in the main bronchus presenting major collapse. The entire procedure will be documented through video recording, and the images will be analyzed with software assistance (Image Processing Toolbox, Matlab). Measures in the airway variation area will be analyzed by comparing the area of collapse at 0 cm H2O pressure with the corresponding measurements at different applied pressures titrated during the procedure. This analysis will allow us to find the pressure that reduces the degree of airway collapse (P2) [42,43]. EIT will be used for impact analysis of different pressures on pulmonary ventilation (distal airways), a functional imaging method that uses low-intensity electric currents. EIT can dynamically evaluate regional pulmonary ventilation by analyzing impedance variations and minimum impedance in a given thoracic segment by reproducing them in two-dimensional images. It is a noninvasive method that does not use ionizing radiation [44-47].

The EIT data will be acquired using ENLIGHT (Timpel), which produces 50 images per second, sampled in real time [44-47]. Distribution of ventilation will be analyzed at each CPAP level during the positive and expiratory pressure (PEEP) titration maneuver by dividing the EIT image into 4 quadrants (regions of interest, ROI), 2 of which will be gravity dependent (lower lobes) and 2 will be gravity independent (upper lobes). In patients who present tracheomalacia during bronchoscopy, a chest CT will be performed at visit 3 during inspiration and forced expiration in the presence or absence of CPAP. The ideal pressure for this will be obtained during bronchoscopy with an aim to evaluate and document the reduction of tracheal collapse. The images will be obtained by multislice tomography. No intravenous contrast will be administrated.

### Statistical Analysis

Because MKS is a rare disease, there will be no sample size calculation. It will be a convenience sample including all eligible patients from Mounier-Kuhn reference centers in Brazil. As of July 2020, we are following at least 15 patients with MKS.

We will perform five main types of descriptive analysis on the data: (1) sociodemographic data of all MKS populations included in the study; (2) comparative analysis of the clinical-functional data of patients with and without collapse; (3) prevalence of sleep apnea/hypopnea syndrome; (4) repeated measurement techniques (bidirectional analysis of variance and Tukey or Sidak post hoc test when there is a difference) correlating the pressure that reverses the collapse (P1 and P2), to analyze the difference between airway collapse that occurs with and without PEEP; and (5) comparisons in the distribution of EIT ventilation with and without PEEP. Statistical analysis will be performed with statistical packages Sigma Stat V3 or SPSS V22, and an α level ≤.05 will be considered significant for all tests.

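### The planned Tukey or Sidak post hoc tests do not match the protocol's question, which is each pressure against 0 cm H2O: over ten levels, all-pairs testing means 45 comparisons where 9 are needed, at a cost in power

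*Protocol article*

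**What the plan says.** All references are to the protocol article.

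- **Statistical Analysis, item (4)** plans a repeated-measures analysis by "bidirectional analysis of variance and Tukey or Sidak post hoc test when there is a difference", with the aim "to analyze the difference between airway collapse that occurs with and without PEEP". The two factors of the ANOVA, the set of post hoc comparisons and the error term are not named. For the whole plan, "an α level ≤.05 will be considered significant for all tests".
- **Study Design, Stage 2** starts the CPAP titration at 0 cm H2O; the pressure is then "gradually increased in steps by 2 cm H2O every 10 complete respiratory cycles until a pressure of 18 cm H2O is reached". The area of collapse at 0 is compared with the area at each of the other pressures, to find the pressure that reduces collapse (P1 by consensus of the bronchoscopists, P2 by image analysis). The titration is repeated in the worse main bronchus.
- **EIT.** Stage 2 says that the distribution of ventilation is examined at every CPAP level. Statistical Analysis, item (5), plans "comparisons in the distribution of EIT ventilation with and without PEEP".
- **Numbers.** There is no sample size calculation. The text says "As of July 2020, we are following at least 15 patients with MKS". Patients without significant collapse in Stage 1 do not go on to titration, and the number expected to do so is not given.

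**The concern.** The question in Stage 2 has a reference level (0 cm H2O) and an order (rising pressure). Tukey's test has neither: it compares every level with every other. Most of the pairs it covers, such as 6 against 14 cm H2O, are not what Stage 2 asks about, yet each makes the threshold stricter for the comparisons that matter. In a rare disease with few titrated patients that price is high. A real difference from 0 that is missed also raises the lowest pressure at which the group can be shown to benefit.

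A second worry depends on details not shown. The pressures follow one another in one continuous ramp, so neighbouring readings are likely to be more alike than distant ones. An uncorrected F test, or a Tukey test with one pooled error, assumes that all differences between levels have the same variance.

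Finally, items (4) and (5) both speak of with and without PEEP, while Stage 2 works level by level. A reader cannot tell whether PEEP enters as two levels or ten.

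**Working it through.** The article states no sample size, power or error rate, so there is no figure to reproduce.

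**Inputs from the document:** pressures 0, 2, ..., 18 cm H2O; alpha 0.05. **Assumptions:** two-sided tests; n = 8, 10 or 15 titrated patients; a mean paired difference of 1.2 times the SD of the paired differences; the serial correlations below.

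**Step 1, counts.** Levels: 18/2 + 1 = 10. All pairs: 10 × 9/2 = 45. Against 0: 9.

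**Step 2, Sidak level per comparison,** 1 − 0.95^(1/m):
- m = 45: 0.00114
- m = 9: 0.00568

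**Step 3, power of one paired comparison.** This is the probability that a noncentral t with n − 1 degrees of freedom and noncentrality 1.2√n exceeds the two-sided critical value.

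| n | 1.2√n | critical t, 45 pairs | power | critical t, 9 vs 0 | power |
|---|---|---|---|---|---|
| 8 | 3.39 | 5.29 | 16% | 3.93 | 40% |
| 10 | 3.79 | 4.69 | 31% | 3.61 | 59% |
| 15 | 4.65 | 4.07 | 70% | 3.26 | 89% |

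**Step 4, the same comparison by simulation.** With AR(1) correlation 0.7, a linear shift of 1 SD from 0 to 18 cm H2O and n = 15, power for 18 against 0 is 0.16 with paired Sidak over 45 pairs and 0.36 over 9. At n = 10 the figures are 0.06 and 0.17. The shift equals a paired effect of 1/√(2(1 − 0.7^9)) = 1/√1.919 = 0.72 SD, so power is lower than in Step 3, but the ordering is the same.

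**Step 5, type I error with no pressure effect** (20,000 simulated trials per setting, n = 8 to 15):
- Uncorrected F: about 5% under equal correlation, 9 to 10% at AR(1) 0.7, 12 to 13% at 0.9.
- Pooled-error Tukey, familywise: about 5% under equal correlation, 6 to 7% at 0.7, about 8% at 0.9.
- Greenhouse-Geisser F: 0.8 to 4.8% across the settings run.
- Paired Sidak: 3.0 to 4.7% over 45 pairs, 2.9 to 4.7% over 9.

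**Step 6, why pooling misleads.** At AR(1) 0.9 with SD 1, the pooled variance of a difference is 0.605. The true value is 2(1 − 0.9^9) = 1.225 for 0 against 18 and 2(1 − 0.9) = 0.200 for neighbouring levels. The pooled standard error is thus √(1.225/0.605) ≈ 1.4 times too small for the widest contrast and √(0.605/0.200) ≈ 1.7 times too large for adjacent ones.

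**The case against.** **The plan may already be adequate.** It does specify repeated-measures techniques and calls its analyses descriptive. The ANOVA factors are unnamed. If PEEP is a two-level factor, there are no 45 pairs, and Sidak can be confined to nine comparisons. This stands: 45 is certain only for Tukey over all ten levels. It does not remove the mismatch, because the article names a test that is all-pairs by construction for a question about differences from 0.

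**The error rates are not shown to be wrong.** A reader might infer that the plan inflates type I error outright. The documents do not support that. Inflation needs both unequal correlation and no correction, and a sphericity correction or covariance structure may well be in an analysis plan that is not shown. Tukey and Sidak are built to hold the familywise rate, so the cost of 45 pairs is power, not alpha.

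**The power gap depends on the error term.** The gain from 45 to 9 is like for like, with paired errors. In the first case of Step 4 (n = 15), pooled-error Tukey has power 0.56, partly because its standard error is too small for that contrast. Under equal correlation of 0.7 with a 1.5 SD shift and n = 10, it reaches 1.00 against 0.98 for paired Sidak over 9. That also stands.

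**A slope should not replace the comparisons.** It is tempting to make one linear trend the main test, since its power is 0.70 in that same case. But a slope does not locate the pressure that reduces collapse. If collapse falls early and then levels off (full 1 SD shift from 2 cm H2O, AR(1) 0.7), the standardised effect of the linear contrast is 0.34 against 0.72 for 18 versus 0.

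**Conclusion.** The point holds as a mismatch between the named post hoc tests and the Stage 2 question. Across the assumed sample sizes, restricting paired Sidak tests to the 9 comparisons with 0 raises power per comparison by 19 to 28 percentage points (16 to 40%, 31 to 59%, 70 to 89%). The n, effect size and correlations are all assumptions.

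The type I error figures are conditional and are not a finding by themselves. Three further inferences are not supported:
- **A ceiling of about 15 patients.** The text says at least 15 are followed. The number titrated may be smaller but is not given.
- **EIT reduced to two conditions.** Item (5) alone suggests this, but Stage 2 states a level-by-level analysis. The two need reconciling.
- **Patients lost through incomplete readings.** The documents give no rate of unreadable levels, and missing-data handling may be specified elsewhere.

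This is a worthwhile, inexpensive improvement, not an error that invalidates the analysis.

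**What to change.** In Statistical Analysis, item (4):
- Name the two ANOVA factors and state that pressure has ten levels.
- Replace all-pairs Tukey or Sidak with the 9 comparisons of each pressure against 0, separately for trachea and main bronchus. Use Holm on paired tests, or a Dunnett-type adjustment from a mixed model with a suitable covariance structure.
- Give each difference with a 95% confidence interval.
- Report a pressure trend as a supporting analysis, not as the single main test.

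In item (5), match Stage 2 by analysing EIT at each level against 0 in the same way.

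The cost is a change of wording. No new data or patients are needed, and SPSS, already named, can fit these models. The one loss is that differences between two non-zero pressures are no longer formally tested; they can still be described with estimates and intervals.

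### Analysis (4) ties the with-versus-without-PEEP test of collapse to P1 and P2, pressures selected because collapse was lower there; the text should require a test over the fixed pressure levels

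*Protocol article*

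**What the plan says.** Only patients with collapse reach the titration: "Patients who do not present significant airway collapse will be excluded from the next step" (Study Design, Stage 1). In Stage 2, "The CPAP titration will start with a pressure of 0 cm H2O and be gradually increased in steps by 2 cm H2O", ending at 18 cm H2O.

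Two pressures come out of that titration (Study Design, Stage 2, text after Figure 1):

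- P1 is set in the room by consensus of the bronchoscopists: "the minor pressure capable of reducing the degree of collapse in the trachea will be defined (P1").
- P2 comes from areas measured by software on the recorded video. The area at 0 cm H2O is compared with the areas at the other pressures, and "This analysis will allow us to find the pressure that reduces the degree of airway collapse (P2").

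Statistical Analysis then lists, as item (4), a two-way repeated-measures ANOVA with Tukey or Sidak post hoc tests, "correlating the pressure that reverses the collapse (P1 and P2), to analyze the difference between airway collapse that occurs with and without PEEP". It adds that "an α level ≤.05 will be considered significant for all tests". No separate breaths, repeat titration or allowance for the selection is named for this item. On numbers it says "Because MKS is a rare disease, there will be no sample size calculation" and "As of July 2020, we are following at least 15 patients with MKS".

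**The concern.** P2 is by definition a pressure at which measured collapse was below its value at 0 cm H2O. If measured collapse at P2 is then tested against measured collapse at 0 on the same recordings, the difference is negative by construction in every patient who has a P2. Such a test can hardly fail, even if CPAP does nothing. P1 carries a weaker form of the problem: it is picked by sight on the same breaths, and sight and measured area are presumably related.

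The Discussion gives as the study's goal to assess whether CPAP can reduce collapse and improve ventilation, and the Results section plans a paper on collapse and the pressure that reduces it. A p value from a test that cannot fail would give that claim no support. The reduction estimated at a selected pressure would also lean towards benefit.

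**Working it through.** The article states no power or error rate for this analysis, so there is no figure of its own to reproduce. The check is what the test does when pressure has no effect.

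**Inputs from the article**
- Pressure levels: 0 to 18 in steps of 2, so 18/2 + 1 = 10 levels, 9 of them non-zero.
- α = .05; sidedness is not stated, so two-sided is assumed.
- At least 15 patients followed; the number reaching Stage 2 is not given.

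**Assumptions**
- 8 to 15 patients in Stage 2.
- Normal noise, either independent across levels or serially correlated (AR(1), coefficient up to 0.7).
- A paired t test stands in for the post hoc contrast.

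**Why chance alone yields a P2.** With independent noise and no effect, the reading at 0 is the lowest of the ten with probability 1/10. So 1 − 1/10 = 90% of patients show at least one lower pressure by chance, about 9 of 10 patients. If every retained difference is negative, the two-sided sign test gives 2 × 0.5^n:
- n = 8: 0.0078
- n = 9: 0.0039
- n = 10: 0.0020

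**Simulation for P2.** For patient i, d_i = (collapse at the selected pressure) − (collapse at 0), and t = mean(d) / (SD(d)/√n). A false positive is p < .05 with t < 0, so the nominal rate in favour of PEEP is 2.5%. Results with independent noise:

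| Rule for P2 | n = 8 | n = 10 | n = 15 |
|---|---|---|---|
| First pressure below the 0 value; patients without one dropped | 90% | 97.6% | 100% |
| Pressure with least collapse | 87% | 95% | 99.6% |

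Across n = 8 to 15 and both noise models, the ranges are:
- First reduction, non-reducers dropped: about 88-100%.
- First reduction, non-reducers kept at 18 cm H2O: about 32-61%.
- Least collapse: about 76-100%.

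Stronger serial correlation lowers the rates further; with a coefficient of 0.8 the least-collapse rule gives 72% at n = 8 and 85% at n = 10.

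**P1.** The selecting quantity is visual and the tested one is measured area. With correlation ρ between them and n = 10, the false-positive rate across the selection rules is:

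| ρ | Rate |
|---|---|
| 0 | 2.5% (nominal) |
| 0.3 | 8-14% |
| 0.5 | 17-34% |
| 0.7 | 33-62% |

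The article gives no ρ. As ρ approaches 1, the rate rises to that for P2.

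**Fixed levels instead.** Under the same null, with independent noise, the omnibus repeated-measures ANOVA over all ten levels rejects in 4.7-5.0% of trials, and any Sidak contrast against 0 in about 3.7-3.9%. One slope of collapse on pressure per patient, tested against zero, rejects in about 5% with independent or correlated noise. Fresh measurements at the selected pressure and at 0 give 5.1% at n = 10.

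**The case against.** The strongest reply is that the circular contrast is inferred. Item (4) never says in so many words that collapse at P1 or P2 will be tested against collapse at 0. Stage 2 describes comparing 0 cm H2O with all the titrated pressures and finding P2 from that comparison. On that reading the ANOVA runs over the fixed levels, P2 is an output, and nothing is circular. This stands: the wording permits it, and the 76-100% figures do not apply to it. But item (4) names P1 and P2 as what the with-versus-without comparison is tied to, so the text does not secure the valid version.

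Other replies:

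- *Post hoc tests run only after a significant overall test.* That protects only if the factor is the ten fixed levels. If the levels are 0, P1 and P2, the overall test is circular too. Tukey and Sidak adjust for comparisons among fixed levels, not for a level chosen on the outcome.
- *The analyses are called descriptive.* The same section names significance tests and applies the .05 level to all of them.
- *P1 is chosen by eye.* Correct. A fall in measured area is not forced, so a reader who inferred near-certain significance for P1 as well as P2 would go beyond the documents.
- *Nothing says non-reducers are dropped from item (4).* Also correct. It is a natural consequence of having no P2, but it is inferred, and keeping them lowers the first-reduction rate substantially.
- *The visit 3 CT is separate evidence.* It is on another day, so item (4) is not the only possible support for efficacy. However, CT is not among analyses (1) to (5).

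**Conclusion.** The point holds in conditional form. On the most direct reading of item (4), the test is circular for P2, with a false-positive rate of about 76-100% under the least-collapse rule and 88-100% under the first-reduction rule with non-reducers dropped, or about 32-61% if they are kept at 18 cm H2O. For P1 the bias has the same direction, but its size is unknown: about nominal to 60% at n = 10 for correlations between sight and measured area of 0 to 0.7. These figures rest on an assumed 8 to 15 Stage 2 patients, normal noise with serial correlation up to 0.7, and a paired t test in place of the ANOVA contrast.

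The documents do not support saying that the plan certainly commits to the circular test, that significance is nearly guaranteed for P1, or that the whole efficacy case rests on this test. They do show a stated analysis that allows a valid and an invalid version and points towards the invalid one, on the central question of the trial.

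**What to change.** Reword item (4):

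1. The test of CPAP effect is a repeated-measures analysis of measured collapse with pressure (0, 2, ..., 18 cm H2O) as a fixed factor or trend, in all patients who enter Stage 2. A per-patient slope tested against zero is a simple form that suits a small sample. If the ANOVA is kept, allow for correlation between neighbouring levels; the 4.7-5.0% above assumes independent noise.
2. P1 and P2 are reported descriptively, with no p value for collapse at P1 or P2 versus 0.
3. State as a limitation that pressure always ascends, so it is confounded with time under sedation. The roughly 5% error of the slope test assumes no drift over the procedure.
4. Use the visit 3 CT as separate-day supporting evidence only after the article is reconciled on who undergoes it. The Abstract says patients with a reduction in collapse; Stage 2 says patients with tracheomalacia. A CT limited to patients who showed a reduction is not an independent check. Note also that CT is taken in forced expiration, whereas the Stage 1 bronchoscopic assessment is in normal ventilation.

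The cost of items 1 to 3 is wording only: the titration already covers all ten levels and is recorded on video, so no new bronchoscopy data are needed. Item 4 needs the two CT statements reconciled.
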